| Study Design                          | Observational Cohort Study                                                                                                                                                                                                                                                                                                                        |                                                                                                                                                                      |
| Study Intervention (where applicable) | N/A                                                                                                                                                                                                                                                                                                                                               |                                                                                                                                                                      |
| Study Participants                    | Adults aged 18+ years consulting general practice for a common musculoskeletal pain condition                                                                                                                                                                                                                                                     |                                                                                                                                                                      |
| Planned Sample Size                   | 
For patient-reported outcomes and experiences: 1,139 patients from 26 practices (completing a baseline questionnaire and consenting to further contact and individual record linkage)
 
For electronic health record (EHR)-only processes of care: 11,388+ patients from 26+ general practices (minimum of 150 patients per practice)
 |                                                                                                                                                                      |

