## **2.1. Primary objectives**

**2.1.1.** To estimate the magnitude and direction of differences between potentially 'disadvantaged' and 'advantaged' groups of patients in their reported MSK health outcomes up to 6 months after consultation [patient-reported outcomes/experiences subcohort]

**2.1.2.** To estimate the magnitude of between-practice variation in rates of primary care (re)consultation, secondary care referral, opioid prescribing, and musculoskeletal imaging for adults consulting with a MSK pain condition [EHR-only processes of care]

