### 7.1.2. EHR-only processes of care outcomes (primary objective 2.1.2)

Our study population will be all adults consulting for a relevant musculoskeletal pain condition over the study period. From the estimates in 7.1.1., we expect an average of 219 patients per practice over a 3-month period. This exceeds the 150 patients recommended as the minimum needed per service for assessing variation between providers using, for example, funnel plots.[35] Smaller practices (list size<5,000) are likely to fall below this target of 150 adult MSK pain consultants over a 3-month period. We therefore intend to extract pseudonymised, record-based outcomes for eligible adults consulting for a MSK pain condition in each practice over 6-month intervals. This will enable practices with list sizes as small as 2500 to meet the target of 150 patients. For 26 practices, this yields a total sample size of roughly 11,388. However, for this component of the study, where the burden on general practices is very low, we will extend the invitation to participate to all general practices in North Staffordshire & Stoke-on-Trent using the EMIS clinical IT system and, if necessary, to other eligible and interested practices in the West Midlands.

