### **7.3.2.2 Primary outcomes analysis**

To determine each practice's case-mix adjusted percentage of patients receiving a process of care we will develop multivariable generalised logistic fixed effect regression models, with general practice as a fixed effect. We will first determine the association of process of care with the different case-mix factors. Each process of care (for example, strong opioid prescription) will be modelled separately, with the other processes of care included as case-mix variables in the model. We will use a backward stepwise selection process to determine which variables should be included in the final model. Those with a *p*-value of 0.20 or less will be retained. Using this model, the predicted probability of receiving the process of care for each consulting patient can be derived, based on the patient's characteristics and the model beta coefficient estimates. Each general practice's expected percentage receiving the process of care will then be determined by calculating the average predicted probability among all musculoskeletal consultants at that general practice. Comparison to the observed percentage indicates each general practice's absolute (observed - expected) and relative (observed/expected) deviation from the expected percentage receiving the process of care.

We will use funnel plots with 95% control limits to plot the case-mix adjusted deviation from the expected percentage across practices, and identify outlying practices. We will repeat the analyses for each 3- or 6-month interval from July 2016 and for specific musculoskeletal conditions (for example, osteoarthritis, back pain).

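### Primary objective 2.1.2 asks how large between-practice variation is, but the planned analysis gives only practice-level deviations and outlier labels, and neither estimates that size

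*Protocol*

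**What the plan says.** Protocol section 2.1 gives primary objective 2.1.2 as "To estimate the magnitude of between-practice variation in rates of primary care (re)consultation, secondary care referral, opioid prescribing, and musculoskeletal imaging" among adults consulting with musculoskeletal pain. The Study Summary repeats it and lists practice-specific rates as the main outcomes.

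The analysis for this objective is in section 7.3.2.2. A logistic model is fitted for each process "with general practice as a fixed effect". A practice's expected percentage comes from "calculating the average predicted probability among all musculoskeletal consultants at that general practice". What is reported for each practice is the "absolute (observed - expected) and relative (observed/expected) deviation from the expected percentage". Then: "We will use funnel plots with 95% control limits to plot the case-mix adjusted deviation from the expected percentage across practices", "and identify outlying practices". The analysis is repeated by time interval and by condition.

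The section names no summary across practices: no between-practice standard deviation or variance, intraclass correlation, median odds ratio or percentile range, and no interval for one. A multilevel model with patients nested in practices appears only in section 7.3.1.2, for the baseline MSK-HQ score.

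On size, section 7.1.2 says "For 26 practices, this yields a total sample size of roughly 11,388". The Study Summary treats this as a minimum: "11,388+ patients from 26+ general practices".

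**The concern.** The objective concerns one number per process: how widely practices' underlying rates differ once case-mix is allowed for. The analysis gives one deviation per practice and a label for some of them. With practice as a fixed effect, the model contains no variance parameter for practices, so the target quantity is never estimated and has no interval.

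A reader of the results would have to infer the magnitude from the scatter of points or from the count outside the limits. The scatter is inflated by sampling error, most of all in small practices. The count rises with the number of patients per practice even when true variation is unchanged. Magnitude could therefore not be compared fairly between processes with different rates, between 3-month and 6-month intervals, or between all consulters and a single condition.

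**Working it through.** **1. The plan's own figure.** Inputs from section 7.1.1: median list size 7,300, 80% adult, 15% annual consultation prevalence.
- 7,300 × 0.80 × 0.15 = 876 consulters per practice per year, so 219 per 3 months and 438 per 6 months.
- 26 × 438 = 11,388, as stated in section 7.1.2.
- A list of 2,500 gives 2,500 × 0.80 × 0.15 / 2 = 150 per 6 months, the plan's minimum.

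The sizes that matter are therefore about 150 to 438 patients per practice and interval.

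**2. Spread from chance alone.** If all practices shared the same true rate p, the standard deviation of observed minus expected would be about √[p(1 − p)/n]. The protocol gives no process rates, so p is assumed over a range.

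| Assumed p | n = 150 | n = 438 |
|---|---|---|
| 5% | 1.8 points | 1.0 points |
| 10% | 2.4 points | 1.4 points |
| 20% | 3.3 points | 1.9 points |
| 40% | 4.0 points | 2.3 points |

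**3. How far the raw spread overstates true variation.** Approximately, the variance of observed minus expected is τ² + p(1 − p)/n, where τ is the true between-practice standard deviation in percentage points. Assume p = 20%. A standard deviation s on the log-odds scale gives τ ≈ s × 0.2 × 0.8.
- s = 0.1: τ = 1.6 points. Raw spread is √(1.6² + 3.27²) = 3.6 at n = 150 and √(1.6² + 1.91²) = 2.5 at n = 438.
- s = 0.2: τ = 3.2 points. Raw spread is 4.6 and 3.7.
- s = 0.5: τ = 8.0 points. Raw spread is 8.6 and 8.2.

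The overstatement is more than twofold for small true variation in small practices, and slight for large variation.

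**4. The count outside the limits is not a measure of magnitude.** Simulation of 26 practices of equal size, 20% rate, expected value from the pooled rate. Entries are the mean number outside 95% limits.

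| Assumed log-odds SD | n = 150 | n = 219 | n = 438 | n = 876 |
|---|---|---|---|---|
| 0.1 | 1.8 | 2.2 | 3.3 | 5.1 |
| 0.2 | 3.9 | 5.0 | 7.9 | 11.3 |
| 0.3 | 6.7 | 8.4 | 12.0 | 15.3 |
| 0.5 | 11.6 | 13.6 | 16.8 | 19.3 |

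With variation fixed at 0.2, the count almost triples from n = 150 to n = 876. Conversely, 0.3 at n = 438 and 0.5 at n = 150 give nearly the same count (12.0 and 11.6).

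**5. The 95% limits (secondary).** With 26 independent practices, a known centre line and no true variation, 26 × 0.05 = 1.3 flags are expected per plot, and the chance of at least one is 1 − 0.95^26 = 74%. With the centre line estimated from the same practices, simulation over rates of 5% to 40% and sizes of 150 to 726 gives about 1.2 flags and 69% to 70%. With 40 practices the formula gives 1 − 0.95^40 = 87%.

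These figures require expected values computed without the practice terms. If the practice terms are kept in the prediction, as section 7.3.2.2 can be read, observed equals expected in every practice (largest difference in a fitted example about 6 × 10⁻¹⁷) and no practice can be flagged.

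**The case against.** The case for the plan has four parts.

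- **Detail for a separate document.** Sections 8.2 and 8.3 mention a statistical analysis plan apart from the protocol, which could name a summary of variation. This stands for the choice among standard deviation, median odds ratio and intraclass correlation. It does not remove the mismatch, because section 7.3.2.2 already fixes the model form, the outputs and the limits, and that form has no variance parameter for practices.
- **The objective is answered in part.** The Study Summary names practice-specific rates as outcomes, the planned deviations are magnitudes for individual practices, and funnel limits show the sampling error expected at each size. This stands. A reader might infer that the objective goes wholly unanswered, which is too strong: it is answered descriptively, without a summary freed of sampling error.
- **Flagging is not the primary target.** Among the objectives, outlier identification appears only as secondary objective 2.2.7. A reader might multiply the chance flags per plot over four processes and every interval since July 2016. The documents do not support using that total against objective 2.1.2: section 6.4 ties the retrospective period to secondary objective 2.2.3, and the total would need an absence of true variation in every plot. Where practices do differ, many points outside the limits reflect real differences.
- **No stated consequence of a flag.** A reader might infer that practices will be named as outliers. Section 11.1 plans aggregate-level reports, objective 2.2.5 seeks stakeholder feedback on visualisations, and no section says that flagged practices will be named.

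Fixed practice effects are also a legitimate choice for estimating single practices. They are not sufficient by themselves for the stated objective.

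**Conclusion.** The point holds as a mismatch between objective and analysis. Followed as written, section 7.3.2.2 gives deviations and labels by practice but no estimate, with an interval, of how much practices vary. The size of the problem depends on the true variation, which the protocol does not state. At an assumed 20% rate, the raw spread overstates a log-odds standard deviation of 0.2 by about 43% at 150 patients per practice (4.57/3.2) and 16% at 438 (3.73/3.2). It does so by more for smaller variation and by less for larger.

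The secondary point is conditional. With 26 practices, no true variation and expected values that leave out practice terms, about 1.2 to 1.3 practices per plot would fall outside 95% limits, with about a 70% to 74% chance of at least one. A point outside those limits should therefore not by itself be called an outlier. The figure is not a forecast of the study's false-flag rate, because it assumes that practices do not differ.

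**What to change.** For each of the four processes, make the primary result for objective 2.1.2 a logistic model with patient case-mix and a practice random intercept. Report the between-practice standard deviation on the log-odds scale, or the median odds ratio or intraclass correlation derived from it, with a 95% interval. Name one of these in advance.

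Keep observed minus expected, observed over expected and the funnel plots as display. State that expected values come from a model or prediction without practice terms. Describe a practice outside 95% limits as one to look at further. Wider limits or an allowance for overdispersion are optional.

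The cost is a little more analysis on data already to be extracted. The drawback is imprecision. Even if each practice's true log odds were known exactly and were normally distributed, 26 practices (25 degrees of freedom, chi-square quantiles 13.12 and 40.65) would give a 95% interval from √(25/40.65) = 0.78 to √(25/13.12) = 1.38 times the estimated standard deviation. Sampling error within practices widens this further. Recruiting beyond 26 practices, which section 7.1.2 already intends for this component, narrows it.

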## **8 DATA HANDLING**

### **8.1. Data collection tools and source document identification**

Patient-reported data are to be captured through a secure online platform (Keele Health Survey) ensuring that all regulatory requirements are met, including the Data Protection Act 2018, UK General Data Protection Regulation (UKGDPR), NHS Information Governance, and Good Clinical Practice (GCP). Data will also be collected via paper questionnaires; these data will be entered manually into the online platform by a Keele CTU administrator. DOCMAIL is a standards-compliant hybrid mail service, providing document management and ISO 27001 secure mailings.

Patient-reported data will be collected at baseline and monthly for 6 months. Following a retrospective search at the GP practice, eligible patients with an active mobile telephone number registered at the GP practice will be sent a SMS text containing a URL link to an online questionnaire. Patients who do not have an active mobile telephone number at the GP practice will be sent an invitation pack including an invite letter, a Participant Information Sheet, a paper questionnaire, and a pre-paid return envelope. All patients who were sent a SMS text will be sent a reminder text approximately 48 hours after the initial text was sent. If patients do not respond after receiving this text reminder, there will be no further contact with them.

With regard to follow-up, patients will be sent one question at 1, 2, 4, and 5 months. This will either be sent via SMS text or a paper questionnaire. Where there is no response to the monthly question, one reminder SMS text or letter will be sent to the participant. If there is still no response from the participant, then they will continue on the follow-up pathway and will be sent the next month's follow-up questionnaire when it is due. A more substantial follow-up will be done at 3 and 6 months, where patients will be sent either a link via SMS text or email to another online questionnaire or posted a paper questionnaire. Where there is no response to the 3- and 6-month follow-up, two reminder SMS texts or emails or a postcard and then a paper questionnaire will be sent to the participant. If there is

still no response from the participant, at 3 months they will continue on the follow-up pathway, at 6 months there will be no further contact as this is the end of the study.

The consenting process will be clearly outlined, and the potential participant will have to agree to the study and what information is being shared (and with whom) after completing the baseline online questionnaire or at the end of the paper questionnaire, to allow the patient to be 100% clear on exactly what information they are consenting to share.

## **8.2. Data handling and record keeping**

Data management will be carried out in accordance with a Study Data Management Plan, adhering to Keele University Standard Operating Procedures (SOPs).

Study data acquired from participants will be stored on Keele University servers and password protected. Data extracted from GP clinical systems and from NHS Digital databases will be stored on Keele University servers and password protected, and linked for the purposes of analysis, or it will remain within the secure data centre of EMIS X, the electronic health record vendor. The latter approach has only recently been put into effect for urgent COVID research in the OpenSAFELY initiative ([OpenSAFELY: Home](#)) but it is believed to attain a higher level of data security and research transparency than previous, conventional approaches to EHR analysis since EHR data remains where it currently resides. Record-level data from NHS Digital will be transferred via secure electronic file transfer. All confidentiality arrangements adhere to relevant data protection regulations and guidelines (Data Protection Act 2018, UK General Data Protection Regulation (UKGDPR), Caldicott, General Medical Council (GMC), Medical Research Council (MRC) UK Policy), Confidentiality NHS Code of Practice, and the Chief Investigator and Study Statistician (Data Custodian) have responsibility to ensure the integrity of the data and that all confidentiality procedures are followed.

All information will be held securely and in strict confidence. Each person who consents to take part in this study will be given a study ID so that data stored from the study will not contain any identifiable information, such as names and addresses. On this basis, these anonymised data will be kept electronically and may be used in other research studies.

The subset of anonymised, non-sensitive data from the locked, validated dataset used to generate the tables, figures, and results for the Final Report to Nuffield Foundation, together with the study protocol, statistical analysis plan, data dictionary, and analysis code, will be made available upon acceptance of the Final Report to the Nuffield Foundation. These datasets will be registered on Keele University's Research Data Repository with a unique Digital Object Identifier (DOI), enhancing its discoverability.

## **8.3. Access to Data**

Keele University is a member of the UK Reproducibility Network and committed to the principles of the [UK Concordat on Open Research Data](#). The School of Medicine and Keele CTU have a longstanding commitment to sharing data from our studies to improve research reproducibility and to maximise benefits for patients, the wider public, and the health and care system.

Metadata, including study protocol, statistical analysis plan, data dictionaries and key study documents (Participant Information Sheet, consent form) will be deposited on a publicly accessible repository if required. De-identified individual participant data (IPD) that underlie the results from this study will be securely stored on servers approved by a government-backed cyber security scheme and made available to bona-fide researchers upon reasonable request via our controlled access procedures. Unless there are exceptional circumstances, data will be available upon publication of

main study findings or within 18 months of study completion (whichever is later) and with no end date. Data requests and enquiries should be directed to [[contact]](mailto:[contact]). We encourage collaboration with those who collected the data, to recognise and credit their contributions.

Any requests for access to the data from anyone outside of the research team (e.g. collaboration, joint publication, data sharing requests from publishers) will follow the Keele University Standard Operating Procedure (SOP) data sharing procedure.

#### **8.4. Data Sharing Agreements**

Record-level data requested by the research team will be shared by NHS Digital subject to a Data Sharing Agreement and in the context of a current, valid Data Sharing Framework Contract.

The data generated from this study will remain the responsibility of the Sponsor. Release of data will be subject to a data use agreement between the Sponsor and the third party requesting the data. De-identified individual participant data will be encrypted on transfer.

The full statement on data sharing can be found at <https://www.keele.ac.uk/informationgovernance/fortheuniversity/dataprotection/datasharing>.

#### **8.5. Archiving**

At the end of the study, data will be securely archived in line with the Sponsor's procedures for a minimum of 10 years after end of study declaration and until the sponsor authorises destruction. Archiving will be carried out in accordance with Keele University SOPs.

### **9 MONITORING & AUDIT**

#### **9.1. Study Management**

The study will be managed by Keele CTU in accordance with Keele University SOPs. The study Chief Investigator (CI) is responsible for the conduct of the study and will convene a Study Management Group (SMG) comprising members of the research team including the PPIE members. Regular meeting of the SMG will take place throughout the study.

The SMG will oversee the protocol completion, obtaining regulatory approval and site set-up and software development. They will be responsible for the delivery of the study, data collection and the ongoing management. The SMG will monitor recruitment procedures, review against timelines and complete regulatory reporting requirements. In addition, they will also oversee the analyses and the interpretation of the results. The SMG will also ensure there is sufficient staffing support available for the study.

The CRN West Midlands, will co-ordinate the general practice identification process and co-ordinate local implementation and study set-up for the research team.

Our experience demonstrates that this combination of detailed plans with regular SMG meetings ensures successful delivery. Good communication across the study will be facilitated by commonly shared study specific and protected drives on the University's network.

Study monitoring will be carried out in accordance with Study Monitoring and Data Management Plans and Keele University SOPs which lay out the procedures for monitoring the data collection, protocol compliance and data management procedures.

